### Trial design

The SExSI-Trial is a pragmatic, assessor blinded, randomised, controlled superiority trial, with a two-group parallel design. Patients will be randomised to either usual care or a home-based intervention consisting of progressive high volume resistance training in addition to usual care with a 1:1 allocation. The primary end-point will be change in patient-reported shoulder function 16 weeks after baseline.

This clinical trial protocol is based on the PREPARE Trial guide [31] and the SPIRIT checklist [32] (Additional file 1). The trial report will adhere to the CONSORT guidelines for reporting parallel group randomised trials, the CONSORT extension for pragmatic trials http://www.consort-statement.org, and the TIDieR template for intervention description and replication [33].

### Interventions

Both groups will receive usual care consisting of an offer of referral to general rehabilitation in the municipal clinic under the Danish health Act § 140, sometimes with the option to instead choose a private physiotherapy clinic, partly at their own expense. The referral is standard procedure when a patient with SIS is considered to have a medically justified need for general rehabilitation, as identified during the examination at the orthopaedic outpatient department (secondary care unit). This procedure is based on the Danish National clinical guideline on diagnostics and treatment of patients with selected shoulder disorders [10], as exercise therapy is recommended as first line of treatment for SIS.

In the context of this study, usual care includes all treatment received by a patient during the time between baseline and follow-up, except that included in ‘Strengthen your Shoulder’. Therefore, usual care might include a range of treatment modalities including advice, stretching, exercises, manual therapy, massage, acupuncture and electrotherapy at the discretion of the treating physiotherapist and doctor. A description of usual care following the TIDieR guidelines [33] is included in Additional file 2.

Patients in the intervention group will, in addition to usual care, receive instructions regarding a home-based, progressive, high volume resistance-training programme immediately after randomisation. Instructions in the exercises are provided at baseline (week 0) and after 2, 5, 10 and 16 weeks. The exercise programme has been developed in cooperation with a team of experts with extensive knowledge of both exercise physiology and rehabilitation and training of patients with shoulder disorders (MC, TB, KT and MR). The design of the exercises, and their progression, is based on the relevant literature regarding exercise physiology, shoulder biomechanics and strength training principles for both healthy people and patients with shoulder disorders. A standard protocol for individual adaptation of the programme based on pain response is part of the intervention.

A thorough description of the intervention, and modifications of the intervention, following the TIDieR guidelines [33], is included in Additional file 3, and the full set of strength training descriptors, as suggested by Toigo and Boutellier [35], are presented in Table 1. An online instruction video of the exercises will be made available upon publication of the main results of the trial, and a link to these is provided in Additional file 3.

**Table 1 Tab1:** Strength training descriptors [35] of the exercises performed in the intervention group

	Phase 1	Phase 2	Phase 3
Load magnitude	15–20 RM	10–15 RM	8–10 RM
Number of repetitions	To volitional muscular fatigue	To volitional muscular fatigue	To volitional muscular fatigue
Number of sets	3 sets	4 sets (2 per exercise)	6 sets (2 per exercise)
Rest in-between sets	60 s	60 s	60 s
Sessions per week	7 per week	3.5 per week	3.5 per week
Duration of experimental period	5 weeks	5 weeks	6 weeks
Contraction modes per rep			
Concentric	2 s	2 s	2 s
Isometric	5 s	5 s	5 s
Eccentric	2 s	2 s	2 s
Rest between reps	2 s	2 s	2 s
Time under tension	9 s	9 s	9 s
Volitional muscular fatigue	Yes	Yes	Yes
Rest between sessions	24 h	48 h	48 h
Anatomical definition of exercise	Yes	Yes	Yes
Range of movement	Exercise 1: 80° ER	Exercise 1: 80° ER Exercise 2: 45° ABD	Exercise 1: 80° ER Exercise 2: 45° ABD Exercise 3: 45° ER

#### Interventions – adherence

Lack of adherence to an exercise intervention is a major problem when aiming at investigating the effect of an intervention. In the previously described studies that include unsupervised resistance training in rehabilitation of SIS patients, monitoring adherence is either done using a log-book filled in by the patients [9, 12] or not described at all [13]. Using only patient-reported measures of adherence may limit the possibility of detecting which exercise dose is actually received by the patient. Accordingly, in a recent systematic review, the authors did not identify a single measure of patient-reported adherence to unsupervised home-based rehabilitation exercises to be sufficiently investigated [36]. Furthermore, findings from one previous study revealed that the dose of exercises reported in exercise diaries were 2.3 times higher than that collected through a system which monitored the exact TUT, being the total time a muscle resists weight during each set [37]. This clearly underlines the relevance of collecting objective data on exercise adherence. In addition, it seems unlikely that patients are always able to ‘take’ precisely the exercise dose prescribed. This issue was unfolded in a recent study, revealing that, just 2 weeks after initial instructions, only 7 out of 29 young healthy individuals were able to use the correct TUT, when performing shoulder exercises with an elastic band [38].

In the SExSI-Trial, adherence to the add-on progressive high volume resistance training intervention will be captured using the BandCizer^©^. The BandCizer^©^ is a small device which is mounted on the elastic band during exercises to measure the TUT, number of repetitions and total work load for all exercises performed. Exactly TUT is a promising objective measure of exercise adherence, for which the BandCizer^©^ is specifically developed and validated [39–41]. By directly monitoring the actual TUT for the prescribed exercises a more precise and objective distinction between adherent and less adherent patients will be possible.

In both the intervention group and the control group, the time spent on exercises related to usual care will be monitored by self-report, using a text-message based system (SMS-track^©^). Each week all participants will receive a text-message question regarding the time spent on exercises performed for their shoulder disorder. Participants in the intervention group will be instructed not to include the time spent on the add-on intervention in this report.

In the intervention group, face-to-face adherence reminders will be given by the investigator administering the intervention at the initial intervention instruction and at each subsequent intervention appointment (week 0, 2, 5, 10 and 16). The reminders will focus on (1) the importance of performing all prescribed exercises and on correct execution of exercises; (2) emphasising that the intervention is an add-on to usual care, and should not be a substitution for this; and (3) counteracting important barriers to ongoing engagement with home exercises, as identified by Littlewood et al. [42], namely the simplicity of the intervention (lack of potential effectiveness), lack of an early appreciable symptom response, when symptoms are reduced to a certain point, and a lack of self-efficacy.

Intervention adherence will further be enhanced by supplying a leaflet with the programme to stick on the fridge, and via the proactive follow-up intervention appointments, aspects known to improve patients adherence to a home-based exercise programme [42]. For an English version of the leaflets, see Additional files 4, 5 and 6.

#### Interventions – concomitant care

Concomitant use of corticosteroid injections will be based on the treating orthopaedic specialist’s evaluation, which is in accordance to the departments standard procedure and in line with the Danish national guidelines for treatment of SIS [10]. For pain relief, concomitant use of orally suspended NSAIDs will be permitted at patients’ own discretion. Corticosteroid injections and use of pain medication will be recorded.

### Outcomes

#### Primary outcome

The primary outcome will be the change in the patient-reported outcome (PRO) score SPADI [43]. SPADI is a widely used shoulder-specific PRO [44], considered one of the most responsive shoulder PROs [45–48], with a minimal clinical important difference (MCID) of 8 to 13 points [45, 48] and a high standardised response mean of 1.38. The SPADI is easy and fast to complete [48] and, in a recent systematic review [49], it was highlighted as one of three PROs for patients with rotator cuff disease for which the psychometric properties are supported by most strong or moderate evidence.

Baseline values for the primary outcome will be collected from patient records, and passed on by the treating physician to the primary investigator, as completion of the SPADI questionnaire is an integral part of the medical examination. Primary outcome data will be further collected at follow-up weeks 5, 10 and 16, with the main analysis conducted for changes from baseline to 16 weeks follow-up, reported as the difference in mean change between groups.

#### Secondary outcomes

Secondary outcome data will be collected at one or more of the time-points (1) baseline assessment, (2) 5 weeks follow-up, (3) 10 weeks follow-up and (4) 16 weeks follow-up. See participant timeline in the SPIRIT diagram (Fig. 1) for further details.

**Fig. 1 Fig1:**
[figure not shown]
Summary of measures to be collected (SPIRIT figure)

For the following secondary outcomes, the main analysis will be conducted for changes from baseline to 16 weeks follow-up, reported as the difference in mean change between groups.Maximum isometric voluntary contraction (MVC) in abduction and external rotation measured using a handheld dynamometer in neutral position (torque in Newton meter per kilo body weight, Nm/kg). Measures of strength relate directly to the intervention.Range of movement (ROM) in active shoulder abduction (0 to 180°), measured using a digital inclinometer, a widely used measure of function in patients with SIS.An average of least pain and average pain experienced during the last week (Numeric Rating Scale: 0–10), a valid and reliable measure of pain [50]. A measure of pain is important, as pain is one of the cardinal complaints associated with SIS [51].Pain catastrophizing (score from 0 to 52), being exaggerated negative thoughts related to experienced or anticipated pain, which might be a risk factor for chronicity [52], measured using the Danish version of the Pain Catastrophizing Scale.Health-related Quality of Life index (EQ-5D-index, range −0.167 to 1.00) measured with the EQ-5D-3 L [53].Health-related Quality of Life Visual Analogue Scale (EQ-5D visual analogue scale, score 0–100, 0 = lowest health-related quality of life) measured with the EQ-5D-3 L [53].

For the following secondary outcomes, the main analysis will be conducted for the outcome at 16 weeks follow-up, reported as the difference between groups at 16 weeks follow-up.Temporal Summation of Pain (TSP), a measure of central excitability (range 0 to 10 cm on electronic Visual analogue scale). A higher degree of TSP has previously been found in patients with unilateral SIS compared to healthy controls [54], and the decrease in TSP after surgical intervention is reported to be associated with the outcome of surgery [26].Conditioned Pain Modulation (CPM), a measure of the attenuated pain response (increase in tolerated pressure) to a painful pressure stimulus during application of another painful pressure stimulus [55]. CPM is a proxy measure of the function of the endogenous analgesia system, and patients with SIS have a lower CPM compared to healthy controls [54].Pressure Pain Threshold (PPT) is a measure of local mechanical hyperalgesia. It measures how much mechanical pressure is needed to elicit the first onset of pain. PPT is measured in kPa as the threshold for first detection of pain. Patients with SIS have lower PPTs in the shoulder region when compared to matched controls, possibly indicating peripheral sensitisation of the nervous system [26].Scapular Dysfunction (yes/no), measured using the modified Scapula Assistance Test, assessing if scapula muscle dysfunction influences the shoulder disorder. The result of the modified Scapula Assistance Test is a judgement of either positive or negative.Scapula Dyskinesia (yes/no), measured using the Scapula Dyskinesis Test, the result of which is a judgment of either positive or negative test.Global Impression of Change, measured on a 7-point Likert scale ranging from ‘Much better, a very important improvement’ to ‘Much worse, an important aggravation’.Patient Acceptable Symptom State, measured as the dichotomous answer (yes/no) to a standardised question regarding the acceptability of the current state of the shoulder symptoms.

Other outcomes of interest will be pain during testing of external rotation MVC, abduction MVC and active abduction ROM, as reported by the participant on a numeric pain rating scale (0 to 10, 0 = no pain), using standardised verbal anchors for the instruction [50].

### Sample size

The sample size estimation is based on the primary outcome SPADI. Studies on patients with SIS have shown standard deviations (SD) for SPADI change score after 11–12 weeks of between 17 [12] and 18.5 [56], while longer durations seem to entail larger SDs, with a SD of 22 reported for SPADI change from 0 to 22 weeks [12]. The latter is similar to our own unpublished data from SIS patients, showing a SD of 22.5 for SPADI change from 0 to 6 months. Based on this previous data, we expect a common SD of 19.5 for SPADI change values from week 0 to 16, the primary outcome. For the purpose of this study, the MCID for SPADI will be considered to be 10 points, based on previous studies [45, 48]. The negative effect that any dropouts will have on the statistical power will, to some degree, be reduced by the use of multiple imputation. However, the imputation of data will not fully redeem this, as multiple imputation can cause an underestimation of the effect and a larger variation in outcomes. Therefore, we aim at having a high power of 95% to verify an effect equal to or higher than the MCID of 10 points on SPADI, at a 5% significance level. To obtain this, a total of 200 patients will be required (100 in each group). This corresponds to a power of 89.7% in case of a 20% dropout and a power of 85.4% in case of a 40% dropout.

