**Fig. 2 Fig2:**
[figure not shown]
Visualisation of changes in SPADI score in the intervention and control group, respectively (example, not based on data)

For comparison of binary outcomes, proportions will be compared using a χ^2^ test, and odds ratio estimates and corresponding 95% CIs will be reported.

Results from analyses comparing IG and CG for all primary and secondary outcomes will be reported in the second paper outlined in the ‘Dissemination policy’ section, except for the results on secondary outcomes regarding pain sensitisation and scapula dyskinesia, which will be reported in the third and fourth paper outlined in the ‘Dissemination policy’ section, respectively.

*P* values will be reported to the fourth decimal. For all tests, a two-sided significance level of ≤ 0.05 will be applied. All analyses will be conducted using up-to-date versions of SPSS and SAS.

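### The stated power of 85.4% at 40% dropout does not follow from the protocol's inputs: 40% dropout gives 79.6%, and 85.4% is the power at 30% dropout

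*Protocol article*

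**What the plan says.** The Sample size section of the protocol article bases the calculation on change in SPADI from baseline to week 16. It takes 10 points as the target difference ("the MCID for SPADI will be considered to be 10 points") and sets the variability with "we expect a common SD of 19.5 for SPADI change values from week 0 to 16". The test is "at a 5% significance level". The section on statistical methods for outcomes makes this two-sided: "For all tests, a two-sided significance level of ≤ 0.05 will be applied".

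The power target is set high, at 95 per cent ("we aim at having a high power of 95"), because dropout is expected to cost power and multiple imputation is expected to recover only part of it. The result is "a total of 200 patients will be required (100 in each group"). The section then gives the power that remains after loss to follow-up: 89.7% with 20% dropout, and "a power of 85.4% in case of a 40% dropout".

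**The concern.** The three power figures do not lie on one curve. Moving from 100 to 80 per group costs 5.3 points (95.0 to 89.7). Moving from 80 to 60 per group is printed as costing only 4.3 points (89.7 to 85.4). In this range each further loss of 20 patients per group should cost more than the last, because power falls faster as the groups shrink. The third figure therefore looked too high.

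This sentence is the only place where the protocol quantifies how well the trial withstands dropout, and dropout is its stated reason for aiming at 95% power. Anyone judging tolerable attrition, or interpreting a null result after heavy loss, would rely on it. An error in the favourable direction makes the trial look better protected than it is.

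**Working it through.** **Inputs, all from the protocol article**

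- Difference Δ = 10 SPADI points (Sample size).
- Common SD σ = 19.5 (Sample size).
- α = 0.05 (Sample size), two-sided (Statistical methods – outcomes).
- 100 per group (Sample size), allocated 1:1 (Allocation).
- Completers per group with dropout fraction w: n = 100 × (1 − w), so 80, 70 and 60 for 20%, 30% and 40%.

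**Formula**

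For a two-sample t-test with n per group, the degrees of freedom are 2n − 2, and the noncentrality parameter is λ = (Δ/σ) × √(n/2), with Δ/σ = 10/19.5 = 0.5128. Power is the probability that a noncentral t variable with parameter λ falls outside ± the 97.5th percentile of the central t distribution.

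**Results**

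| Dropout | n per group | λ | Critical t | Power (t-test) | Power (normal approximation) | Protocol |
|---|---|---|---|---|---|---|
| 0% | 100 | 3.626 | 1.972 | 95.04% | 95.2% | 95% |
| 20% | 80 | 3.243 | 1.975 | 89.68% | 90.0% | 89.7% |
| 30% | 70 | 3.034 | 1.977 | 85.38% | 85.9% | not given |
| 40% | 60 | 2.809 | 1.980 | 79.56% | 80.2% | 85.4% |

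The t-test reproduces the first two protocol figures to the decimal, which identifies the method used. The same method gives 79.6% at 40% dropout.

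**Working backwards**

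- The n per group that gives 85.4% power is 70.05, which is 30% dropout.
- The SD that would give 85.4% with 60 per group is 18.03, not the stated 19.5.

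**Could another convention give the printed pair?** A candidate must return both 89.7% at 20% dropout and 85.4% at 40%.

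| Convention | 20% dropout | 40% dropout |
|---|---|---|
| Two-sided t-test, completers | 89.7% | 79.6% |
| Two-sided, normal approximation | 90.0% | 80.2% |
| One-sided t-test | about 94% | about 87% |
| Dropout in one arm only (100 vs 80; 100 vs 60) | 92.5% | 87.7% |
| n = 100/(1 + w), i.e. 83.3 and 71 per group | 90.8% | 85.9% |

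None does. The last row comes near 85.4% but misses the 20% figure, and dividing by 1 + w is not a valid way to count those retained.

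**Size of the discrepancy**

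- Power: 85.4 − 79.6 = 5.8 percentage points.
- Type II error: 100 − 79.6 = 20.4% against 100 − 85.4 = 14.6%, a ratio of 20.4/14.6 = 1.4.

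**Sensitivity to the SD.** The section cites SDs of 17 to 18.5 at 11–12 weeks and 22 to 22.5 at 22 weeks to 6 months. With 60 per group the power is:

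| SD | 17 | 18.5 | 19.5 | 22 | 22.5 |
|---|---|---|---|---|---|
| Power | 89.2% | 83.6% | 79.6% | 69.5% | 67.5% |

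None of the cited SDs gives 85.4% at 60 per group.

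**The case against.** The strongest defence is that completer-only power is not the power of the planned analysis. The protocol will impute missing outcomes from earlier scores and fit a constrained linear mixed model to the repeated measurements, so true power at 40% dropout could differ from 79.6%. That is correct, and 79.6% should be labelled as completer-only power. It does not rescue the printed figure. The 20% figure equals completer-only power with no credit for imputation, and the protocol quantifies no such credit that could apply at 40% alone.

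A second point is that the power may be right and the dropout rate wrong, with 40% printed for 30%. The exact match at 70 per group makes this plausible, and the document cannot settle it. The pair is wrong in either case.

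A third is that little depends on the sentence. The sample size comes from 95% power at full enrolment, which reproduces, and 40% dropout is the more extreme of two illustrations. This stands as a limit on the consequences. Nor should much be made of crossing 80%: the t-test gives 79.6%, the normal approximation 80.2%, and the protocol sets no floor at 80%. The fair summary is about 80%, not 85%.

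Finally, the SDs of 22 and 22.5 belong to longer follow-up than 16 weeks. Quoting only those would be one-sided, so the whole cited range is shown above.

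**Conclusion.** The concern holds. On the protocol's stated inputs and the method that reproduces its other two figures, 40% dropout leaves 79.6% power, not 85.4%, and 85.4% belongs to 30% dropout. As written, the sentence overstates power by 5.8 percentage points and understates the type II error (14.6% instead of 20.4%).

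This rests on equal dropout in both arms, an SD of 19.5, a true difference of 10 points and analysis of completers by a two-sided t-test at 5%. The sample size, the 95% headline power, the 20% scenario, the planned analysis and the type I error are not affected.

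**What to change.** Replace the final sentence of the Sample size section with one that is right whichever entry was mistyped, for example: *Counting completers only, this corresponds to a power of 89.7% with 20% dropout, 85.4% with 30% dropout and 79.6% with 40% dropout.* Stating the completer-only basis makes clear that no gain from multiple imputation is included.

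The cost is one corrected sentence and one less favourable figure. The sample size, conduct and analysis do not change.

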### Recruitment strategies

All participants will be recruited consecutively from the arthroscopic centre at the orthopaedic department, Hvidovre Hospital immediately after undergoing clinical examination performed by an orthopaedic specialist, who will also make the initial eligibility screening and provide written information about the trial for eligible patients. In order to achieve adequate enrolment, the orthopaedic specialists, who are at the first line of recruitment, will be informed about the progress of the trial at regular formal and informal meetings.

### Procedures and data collection methods

At baseline, after written consent is signed and before randomisation, all baseline assessments (Fig. 1) will be conducted by clinical physiotherapists who are trained in all assessment procedures and mutually aligned in order to improve the quality of data. All post-allocation assessments (week 5, 10 and 16) will be performed by the same group of testers in order to secure consensus regarding the instructions in questionnaires and conduction of tests. Participants will be instructed not to take any pain medication during the 8 hours prior to any assessment. Outcome assessors will also be trained in counselling for adherence to follow-up testing (to facilitate retention) and avoidance of disclosing allocation in a uniform manner. The study instruments are all described in detail in Additional file 7.

In general, once a participant is enrolled, every reasonable effort will be made to collect all outcomes for that participant, regardless of any deviations from the intervention protocol. Participants will receive text-message reminders for all scheduled follow-up appointments. The weekly text-messages with standardised questions regarding exercise time will also ensure that participants keep in mind their participation in the study. If participants do not attend their scheduled follow-up assessment, they will be contacted and offered to re-schedule to another date. If a participant should withdraw consent to follow-up assessments, the participant is offered the option to continue with the assessment of PROs.

Reasons for non-adherence to add-on intervention will be recorded by the investigator providing the intervention, either at the intervention visits or by phone if the participant does not come to the scheduled appointment. Reasons for non-retention will be recorded by the outcome assessor if this participant withdraws during a follow-up session, or by the primary investigator in a telephone interview.

